## Abstract

**Introduction:**

Mental health services are stretched in the UK and are in need of support. One approach that could improve mental health symptoms is osteopathy. Research suggests that osteopathy influences psychophysiological factors, which could lead to improvements in mental health. The first objective of this protocol is to investigate the feasibility and acceptability of four osteopathic interventions. A secondary aim is to evaluate the interventions’ effectiveness for improving psychophysiological and mental health outcomes.

**Methods and analysis:**

This study will be an explanatory mixed-methods design. Participants will be 30 adults who have mild to moderate mental health symptoms and not experiencing any issues with pain. The feasibility and acceptability of the interventions will be the primary outcomes. Secondary outcomes will be physiological measures including heart rate variability, interoceptive accuracy and blood pressure. Psychological outcomes, collected preintervention and postintervention, will also be measured by five standardised questionnaires, which include: (1) the Depression, Anxiety and Stress Scale (DASS); (2) the International Positive and Negative Affect Schedule-Short-Form; (3) Acceptance and Action Questionnaire-II; (4) the Self as Context Scale and (5) and the Multidimensional Assessment of Interoceptive Awareness Version 2. Participants will be randomised to one of four intervention groups and receive a single intervention treatment session. These intervention groups are: (1) high-velocity and articulation techniques, (2) soft-tissue massage, (3) craniosacral techniques, and (4) a combination of these three approaches. Mixed design two (preintervention and postintervention) by the four interventions analysis of covariance models will be used to analyse the quantitative data for each quantitative measure. Participants will also be interviewed about their experiences of the study and interventions and a thematic analysis will be used to analyse this qualitative data. This will aid the assessment of the feasibility and acceptability of the study design.

**Ethics and dissemination:**

The protocol for this feasibility study has received ethical approval from the Department of Psychology Ethics Committee at Swansea University, ethical review reference number: 2022-5603-4810. Feasibility results from this protocol will be published in a peer review journal and presented at both national and international conferences.

**Discussion:**

This study will assess the feasibility and acceptability of conducting osteopathic interventions for improving mental health outcomes. The results from this will help to inform the development of a future randomised controlled trial. The study will also produce original data which could provide preliminary evidence of whether osteopathic approaches are of benefit to individual’s mental health in the form of effect sizes, even if they are pain-free.

**Trial registration number:**

NCT05674071.

STRENGTHS AND LIMITATIONS OF THIS STUDYThis study will investigate the utility of osteopathic techniques for improving mental health, in the absence of any existing pain.The techniques being compared are based on previous literature and evidence.Due to this being a feasibility study, only a small number of participants are being recruited which will lead to low statistical power of the results.As the study is focused on comparing four interventions in a feasibility setting, there will be no control group comparison.

## Introduction

### Background and rationale

In the UK, mental health problems such as anxiety and depression are an increasing burden within society. Recent estimates suggest that one in six people in the UK experience symptoms of depression or anxiety in any given week.^1^ For the individual, poor mental health can bring about problematic coping behaviours such as substance abuse and self-harm, leading to poor social relationships and in the worst cases; suicide.^2^ Mental health problems are commonly treated through psychotherapeutic means such as cognitive–behavioural therapy, acceptance and commitment therapy, as well as relaxation techniques such as mindfulness practice and yoga.^3^ In addition, pharmacological solutions such as antidepressants and beta-blockers are used in treatment. These approaches have demonstrated effectiveness in many cases though they treat the symptoms and not the underlying causes.^4 5^

With such a high demand being placed on the health services, such as these traditional forms of care, it can be difficult for many to receive treatment.^6 7^ It may, therefore, be important and helpful to consider innovative approaches that could support the demand for mental health services.^8^ Recently, it has been suggested that osteopathic interventions could be one such approach to support mental health services.^9 10^

Osteopathy is an approach to healthcare that uses manual techniques to diagnose and treat patients.^11^ Osteopathy is an Allied Health Profession in England and osteopaths in the UK are regulated by statute.^12^ An osteopathic approach is patient-centred and focused on the patient’s health rather than disease-centred. The practices are evidence-informed and scientific rigour forms an important part of treating patients and managing cases.^13^ Osteopaths use manual contact to identify and evaluate movement in all structural and functional aspects of the patient, identifying alterations of function and movement that impede health and addressing these. Osteopaths use a variety of techniques to manipulate joints, muscles and tissue. All of the techniques used have an effect on the interplay between the nervous and musculoskeletal systems.^14–16^ Specific techniques include myofascial release, lymphatic drainage, high-velocity, low amplitude, articulatory techniques and muscle energy techniques.

The rationale for linking mental health with physiological mechanisms comes as previous studies have examined how osteopathy may influence psychophysiological factors. A number of these have examined the influence of osteopathic manipulative therapy (OMT) on heart rate variability (HRV), which is considered a potentially important indicator of physical and psychological well-being.^17 18^ Cerritelli *et al*^19^ found that two sessions of OMT significantly increased HRV in healthy adults, relative to a sham control group. Similarly, Arienti *et al*^20^ found that applying a single session of fourth ventricle compression (CV4) significantly increased HRV, compared with a placebo intervention. So, there seems to be some clear evidence that influencing physiological mechanisms through osteopathy is highly relevant for mental health improvement. Indeed, studies have found that osteopathic interventions have led to improvements in mental health outcomes such as anxiety,^21^ depression^22^ and stress.^23^ However, few studies have sought to examine the effects of osteopathy on both physiological and psychological outcomes.

This feasibility protocol (that has followed the Standard Protocol Items: Recommendations for Intervention Trials (SPIRIT) guidelines, see online supplemental material 1)^24^ will, therefore, explore both the potential psychological and psychophysiological changes that occur after osteopathic treatment, in a small group of individuals who suffer from mild to moderate forms of anxiety, stress and depression.

10.1136/bmjopen-2023-071680.supp1Supplementary data

### Choice of comparators

This study will be comparing four osteopathic interventions: (1) articulation and high-velocity thrust (AHVT) techniques, (2) soft-tissue massage (STM), (3) craniosacral techniques (CST) and (4) a combination of all three techniques.

The choice of techniques in this study has been informed by a systematic review and meta-analysis by the authors into the impact of osteopathic interventions on psychophysiological factors (This systematic review has been preregistered on Open Science Framework (OSF) and the protocol is available via this link: https://osf.io/jrtpx/?view_only=63ffa916b76c4b95b4233d3cd812f12d). This review included randomised controlled trials (RCTs) of manual interventions and their effects on factors including mental health outcomes and physiological indicators such as HRV and interoception. Articulation techniques were found to improve psychological outcomes,^25 26^ as well as autonomic nervous system indicators such as HRV and interoception.^19^ Similarly, interventions utilising HVT improved interoceptive accuracy (IAc) and led to greater activation of brain areas associated with the interoceptive pathways.^27^ The studies that suggested articulation could improve psychological outcomes were conducted with chronic pain patients and the study on HVT with healthy participants. It will, therefore, be useful to understand whether articulation techniques and HVT could have positive psychological effects in the absence of pain and in the presence of mild mental health symptoms.

Next, STM techniques were chosen. Studies show that this approach has several positive psychological impacts for individuals with chronic pain^22^ and pain-free patients who have mental health diagnoses.^21 28^ Massage therapy has also been shown to have a preventative effect for general stress and well-being.^23^ Lastly, massage techniques have been shown to induce autonomic relaxation in healthy participants by increasing HRV.^29^

The third intervention will use CST. Three studies suggested that this approach induces autonomic relaxation by increasing HRV. One of these studies was conducted with patients with chronic pain^30^ and two were carried out with healthy participants.^20 31^ It will, therefore, be useful to see whether any potential autonomic changes from CST translate to psychological benefits. It will also be useful to examine the potential utility of these techniques with participants who have mild mental health symptoms.

The body areas that each intervention will focus on have also been informed by the aforementioned literature. The interventions will operate on a standardised protocol whereby body areas will be worked on in order by the practitioner. The body areas focused on and the order they will be worked on will be described further in the specific procedures of each intervention.

### Objectives

This study aims to investigate the feasibility and acceptability of four osteopathic interventions for adults with mild to moderate mental health symptomatology. A secondary aim is to evaluate the influence of these four interventions on physiological factors including HRV and interoception. The study will aim to evaluate their effectiveness in improving psychological outcomes including depression, stress, anxiety, negative affect (NA) and psychological flexibility. It is first hypothesised that the interventions will be feasible and acceptable to participants. It is also hypothesised that the interventions will induce psychophysiological relaxation by significantly increasing HRV and improving IAc. No specific predictions are made about blood pressure (BP) as data on this is only being collected to check that we are within safe BP bounds, that is, for participant safety. A final hypothesis is that the four interventions will lead to similar improvements in depression, anxiety, stress and NA.

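### With four active arms and no control, the HRV, interoception and mood hypotheses rest on a pre-post change that cannot be attributed to the interventions

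*Protocol article*

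**What the plan says.** The Objectives section of the protocol article puts feasibility and acceptability first and then adds effect aims. For physiology: "A secondary aim is to evaluate the influence of these four interventions on physiological factors including HRV and interoception". For psychology: "The study will aim to evaluate their effectiveness in improving psychological outcomes". The Introduction of the Abstract also states the secondary aim in terms of effectiveness.

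Two effect hypotheses follow in Objectives. One is that "the interventions will induce psychophysiological relaxation by significantly increasing HRV and improving IAc". The other is that "the four interventions will lead to similar improvements in depression, anxiety, stress and NA".

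Choice of comparators describes the design: "This study will be comparing four osteopathic interventions". The strengths and limitations box adds that "there will be no control group comparison". Statistical methods (Outcomes) plans seven mixed models, each crossing two time points with four arms, with psychotherapy and drug treatment as yes/no covariates. The Discussion of the Abstract says that the data could give "preliminary evidence of whether osteopathic approaches are of benefit", in the form of effect sizes.

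**The concern.** The words used for the secondary aims are causal, and the HRV and interoceptive accuracy hypothesis is also tied to statistical significance. The design has no untreated, sham or rest comparison to support a causal reading. The protocol's own rationale cites a trial in which manipulation "significantly increased HRV in healthy adults, relative to a sham control group", and another with a placebo comparison. The supporting evidence thus came from the kind of contrast that this study lacks.

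At stake is what a significant pre-post change may be taken to mean. As Objectives is worded, a rise in HRV across all arms would satisfy the hypothesis even if lying quietly, doing the task a second time or expecting benefit had produced it. Nothing in the article limits the time effect to a descriptive reading.

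**Working it through.** **No planned figure to reproduce.** The sample size of 32 is justified by feasibility practice, by being about 10% of a full trial, and by resources. No alpha, power, effect size or SD is given. The arithmetic available is 32/4 = 8 per arm.

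**Step 1: which model term carries which hypothesis.** The article names no term, so this follows from the structure of the 2 x 4 model.

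| Term | What it compares | Protected by randomisation? | Bears on |
|---|---|---|---|
| Arm x time | Change under one technique against change under another | Yes | Whether improvements are similar across arms |
| Time (averaged over arms) | After against before, in everyone | No | Whether HRV, interoceptive accuracy and mood improve at all |

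The mood hypothesis predicts similar improvement everywhere, so it expects little in the arm x time term. The predicted benefit then lies wholly in the time term.

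**Step 2: rival explanations with a basis in the text.**
- Rest: the post-treatment measures follow a session of about 30 minutes (Interventions), and HRV is recorded supine on both occasions (Heart rate variability).
- Repetition: the same heartbeat-counting task and questionnaires are given before and after the session (Interoceptive accuracy; Participant timeline).
- Expectation: participants know which intervention they receive (Blinding) and report their own psychological outcomes.

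Each can act in all four arms and so adds to the time term.

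**Step 3: illustration of size.** Assumptions not in the protocol: two-sided alpha 0.05; zero treatment effect; the same non-specific drift d in every arm, in SDs of the change score.

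- Noncentrality = d x sqrt(32).
- Error df = 32 - 4 arms - 2 covariates = 26; critical t = 2.056.
- P(significant) = P(|T| > 2.056), with T noncentral t on 26 df.

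| d | Noncentrality | P(time effect significant) | P(arm x time significant) |
|---|---|---|---|
| 0 | 0 | 0.05 | 0.05 |
| 0.2 | 1.13 | 0.19 | 0.05 |
| 0.3 | 1.70 | 0.37 | 0.05 |
| 0.5 | 2.83 | 0.78 | 0.05 |

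Using 28 df (no covariates) changes these by less than 0.01. A simulation of 20,000 studies on 28 df gave 0.378 at d = 0.3 and 0.785 at d = 0.5, with arm x time at 0.053 and 0.050.

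**Step 4: sensitivity to covariate coding.** The figures above hold if the time effect is evaluated at average covariate values. If the yes/no covariates enter uncentred as 0/1, the time effect is tested for people with neither treatment, and precision falls. With an assumed 25% prevalence of each, the range for d = 0.2 to 0.5 becomes about 13% to 53%. With 40% it is about 11% to 40%.

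**Step 5: would a small control arm settle it?** With 8 controls, the approximate 95% CI half-width for a standardised difference is 1.96 x sqrt(1/8 + 1/8) = 0.98 SD against one arm, or 1.96 x sqrt(1/32 + 1/8) = 0.77 SD against all 32 pooled. That would be too imprecise to rescue the hypotheses, which favours changing the claim over changing the design.

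**The case against.** The strongest reply is that this is a feasibility study that already discloses both the missing control and its low power, makes feasibility and acceptability primary, and describes the psychological and physiological measures as initial data. That is true, and it limits the point to the secondary aims. It does not answer it: disclosure does not make a causal hypothesis testable, and Objectives keeps the causal wording without qualification.

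Four stronger readings are tempting, and the documents do not support them.

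- A reader might infer that the effect sizes will be used to size the later trial. The Discussion of the Abstract links the future trial to the feasibility and acceptability results. Effect sizes come in a separate sentence, hedged with the word could, and no section plans to use them for sample size.
- A reader might suppose that participants lie down for most of every session. Only the soft-tissue arm is described as prone and supine throughout. The articulation arm gives about 10 minutes, and the combined arm about 9, to examination that includes active movement.
- A reader might take 19% to 78% as an inflated false-positive rate. If there is real drift, the hypothesis of no pre-post change is false, and the test is right to reject it. The fault lies in attributing the change to treatment.
- That a significant time effect will be reported as proof of benefit is a prediction. The article leaves room for it but does not state it.

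It is also fair that no drift size comes from the protocol. The conclusion rests on the structure of the design and not on those values.

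**Conclusion.** The point stands for the secondary aims and for both effect hypotheses in Objectives. The design can compare four techniques with one another. It cannot show that any of them, or all together, cause a change in HRV, interoceptive accuracy or mood, because a shared change is not separable from rest, repetition and expectation. The stated limitation does not resolve this while the causal wording remains.

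The size is illustrative: a significant time effect in about 19% to 78% of studies with no treatment effect, for an assumed drift of 0.2 to 0.5 SD of change, an assumed two-sided 5% level, 32 participants and covariates evaluated at their averages. Uncentred covariates would lower these percentages without changing the logic. The primary feasibility and acceptability outcomes are not affected.

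**What to change.** Add no arm.

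1. In the Abstract (Introduction) and Objectives, reword the secondary aim, the HRV and interoceptive accuracy hypothesis, and the final mood hypothesis along these lines: to estimate pre-post change in each arm, and differences in change between arms, with 95% confidence intervals. The mood hypothesis must be included, since it is as causal as the physiological one.
2. In Statistical methods (Outcomes), state that the time main effect will not be read as a treatment effect.
3. In the Abstract (Discussion), describe the effect sizes as uncontrolled pre-post changes and not as evidence of benefit.
4. Because the study began on 20 December 2022, list the change as required under Protocol amendments.

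The cost is an amendment entry and a weaker claim for the secondary results. No extra participants or measurements are needed.

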### Trial design

This is a feasibility study, which will use an explanatory sequential mixed-methods approach. In this approach, the quantitative aspect forms the first part of the study, followed by a qualitative aspect to help provide further explanation and depth.^32^ For the quantitative aspect, the study will use a parallel, randomised design with an equal proportion of participants allocated to each of the four conditions. The qualitative aspect will be completed by interviewing the participants of the intervention and the practitioner delivering them.

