### Sample size

The study will aim to recruit 32 participants. This number of participants is generally deemed sufficient for feasibility studies^48^ and would represent approximately 10% of the sample size required in a full trial.^49^ This sample size also falls within what is practical given the available resources.

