## Methods: assignment of interventions

### Allocation

#### Sequence generation

Thirty-two participants will be randomly assigned to one of the four conditions using a computerised random number generator. Permuted block randomisation will be used to ensure that equal numbers of participants are in each condition. The block sizes will not be disclosed to help ensure concealment and prevent any potential prediction of group allocation. This will be conducted by the principal investigator (PI) of the study [name], while the outcome assessor [name] is blinded to this randomisation process.

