## Statistical methods

### Outcomes

Statistical analysis will be conducted using IBM SPSS (V.27). Means and SD will be reported for demographic data that includes gender, age and ethnicity. For the main analysis, data will first be examined for normality using the Shapiro-Wilk test. If data are skewed, logarithmic transformation will be used, otherwise, analysis will continue without any transformation. HRV data will be preprocessed, and inspected for any potential artefacts, and these will be removed if identified. RMSSD will be calculated on the preprocessed artefact removed data using Kubios V.3.5 (https://www.kubios.com/) via Matlab V.R2021a. IAc will then be calculated using the formula: IAc=1/4 Σ [1−(|recorded heartbeats−counted heartbeats|/recorded heartbeats)]. The psychometrics will be totalled according to the relevant questionnaire instructions and subscales.

The main analysis will comprise of seven separate mixed design two (preintervention and postintervention) by four (AVHT, STM, CST, combination (please see: Interventions section for full details of these interventions.)) analysis of covariance (ANCOVA) models. This will comprise of five separate ANCOVAs for the five psychometrics (DASS, PANAS-SF, AAQ, SACS, MAIA) and another two ANCOVAs for the physiological measures of IAc and HRV (as measured by RMSSD and LF/HF ratio). Covariates will consist of (1) whether participants are currently receiving psychotherapy (yes or no) and (2) whether participants are receiving pharmacological treatment (yes or no). Significant models will be examined further using post hoc Bonferroni tests.

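### The protocol hypothesises similar improvement in four arms but plans only tests for difference, with no margin and eight participants per arm

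*Protocol article*

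**What the plan says.** The last hypothesis in the Objectives reads: "A final hypothesis is that the four interventions will lead to similar improvements in depression, anxiety, stress and NA". It has two parts: that scores improve, and that they improve about equally in the four arms. The article does not say how close counts as similar.

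Statistical methods, Outcomes, sets the main analysis as separate mixed ANCOVAs, two time points by four arms, with two yes/no covariates (psychotherapy and drug treatment). It then adds: "Significant models will be examined further using post hoc Bonferroni tests". It gives no equivalence test and no confidence-interval criterion.

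On size, the Sample size section says "The study will aim to recruit 32 participants", and Sequence generation agrees: "Thirty-two participants will be randomly assigned to one of the four conditions using a computerised random number generator". Trial design specifies "a parallel, randomised design with an equal proportion of participants allocated to each of the four conditions". That makes 8 per arm. The abstract differs: "Participants will be 30 adults who have mild to moderate mental health symptoms and not experiencing any issues with pain".

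The abstract's Discussion says the data could give "preliminary evidence of whether osteopathic approaches are of benefit to individual’s mental health in the form of effect sizes". The list of strengths and limitations concedes low power and says that "there will be no control group comparison".

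**The concern.** A test for difference puts no difference in the null hypothesis. Failing to reject that null shows only that the data did not contradict it. When the research hypothesis is itself one of similarity, the usual effect of a small sample is reversed: low power normally makes a hypothesis harder to support, whereas here it makes a result that seems to agree with it more likely. The admission of low power in the limitations does not address this reversal.

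The protocol article fixes both the hypothesis and the test, so the mismatch is not a detail left to an analysis plan. At stake is how the between-arm result is used. It is the only randomised comparison in the study, and the results are meant to inform a later randomised trial. If a wide and inconclusive comparison is taken as agreement between techniques, that trial starts from a belief the data cannot support.

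A second, smaller point concerns wording. The Objectives speak of effectiveness and of interventions leading to improvement. Without a control arm, the pre-post part of the model estimates change from before to after treatment and nothing more specific.

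**Working it through.** **The plan's own figure.** The total of 32 comes from feasibility convention and a share of about 10% of a full trial, not from a power calculation, so there is no power figure to reproduce. 32 / 4 = 8 per arm is consistent with equal allocation.

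**Inputs.** From the protocol article: 4 arms, 8 per arm, 2 binary covariates, so error df = 32 − 4 − 2 = 26. Assumed, because not stated: two-sided alpha 0.05. Effects are first expressed in SDs of the change score, on which the arm-by-time test is a comparison of four mean changes.

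**Precision for one pair of arms.** Half-width = t × sqrt(2/8) = t × 0.5.
- 95% interval: 2.056 × 0.5 = 1.03 SD.
- Bonferroni for six pairs: 2.856 × 0.5 = 1.43 SD.
- 90% interval, which corresponds to two one-sided 5% tests of equivalence: 1.706 × 0.5 = 0.85 SD.

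So even an observed difference of exactly zero would leave true differences of up to about 0.85 SD unexcluded.

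**Power of the arm-by-time test.** Noncentral F with 3 and 26 df and noncentrality 32 × f².

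| Cohen's f | Noncentrality | Power |
|---|---|---|
| 0.25 | 2.00 | 17% |
| 0.40 | 5.12 | 39% |
| 0.63 | 12.7 | 80% |

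**One arm differing from the other three by d.** Here f = d × sqrt(3)/4.
- d = 0.5: f = 0.217, power 14%, missed 86% of the time.
- d = 0.8: f = 0.346, power 30%, missed 70%.
- d = 1.0: f = 0.433, power 45%, missed 55%.

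**Pairwise power at 0.8 SD.** Noncentral t, 26 df, noncentrality 0.8 × sqrt(8/2) = 1.6: 34% unadjusted and 13% at 0.05/6.

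**Dependence on the SD scale.** If 0.8 SD means the SD of the raw score, the SD of change is sqrt(2(1 − r)) raw SDs, where r is the pre-post correlation. The protocol gives no r, so a range is needed.

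| r | SD of change (raw SDs) | 0.8 raw SD in change SDs | Unadjusted pairwise power | Arm-by-time power, f = 0.40 on raw scale |
|---|---|---|---|---|
| 0.5 | 1.00 | 0.80 | 34% | 39% |
| 0.7 | 0.77 | 1.03 | 51% | 61% |
| 0.8 | 0.63 | 1.26 | 68% | 80% |

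**What showing similarity would take.** Two one-sided tests at 0.05 each, 80% power, true difference zero: n per arm = 2 × ((1.645 + 1.282)/margin)². The margins are assumptions.
- 0.5 SD of change: 69 per arm, 276 in all.
- 0.8 SD: 27 per arm, 108 in all.
- 1.0 SD: 18 per arm, 72 in all.

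With 8 per arm, the simulated chance of showing equivalence for one pair is close to 0% at 0.5 SD, 4% at 0.8 SD and 25% at 1.0 SD.

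**If the total is 30**, as in the abstract, arm-by-time power falls slightly, to 16% at f = 0.25 and 37% at f = 0.40 (7.5 per arm on average).

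**The case against.** The strongest reply is that this is the last of several secondary hypotheses in a feasibility study. Its primary outcomes are feasibility and acceptability, it admits low power, and it offers only preliminary evidence. That stands, and it limits the weight of the point. It does not remove the mismatch between the hypothesis and its test.

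Four stronger readings are tempting, and the article does not support them.

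- *The authors will report a non-significant result as similarity.* The article never says how such a result will be interpreted. What can be said is that no other planned result could support the similarity part.
- *The hypothesis would be confirmed whatever the truth.* It also requires improvement, and the mixed model tests the pre-post main effect across all participants. With 32 participants and 26 df, a mean change of 0.5 SD of change has noncentrality 0.5 × sqrt(32) = 2.83 and power of about 78%. Nor is non-rejection of the arm-by-time test close to certain: it is 83% at f = 0.25 and 61% at f = 0.40, and lower on the raw-score scale with a high pre-post correlation.
- *Only large effects will be reported.* The restriction to significant models applies to the post hoc tests. It does not bar reporting means or effect sizes for every outcome, and the abstract promises effect sizes.
- *A later trial will drop or pool arms on this basis.* No such rule is stated.

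The missing control arm is already declared as a limitation. Only the wording of the aims remains to be aligned with it.

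**Conclusion.** The point holds as a mismatch between a stated hypothesis and the test provided for it. Similarity is predicted, no margin defines it, and only tests for difference are planned. A non-significant arm-by-time result is therefore the only planned outcome that could agree with the similarity part.

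On the change-score scale, that result is likely even when arms differ: power is 17% to 39% for f of 0.25 to 0.40, and a single arm differing by 0.8 SD is missed about 70% of the time. On the raw-score scale the conclusion weakens as the pre-post correlation rises, with unadjusted pairwise power at 0.8 SD running from 34% (r = 0.5) to 68% (r = 0.8). The interval width does not depend on any assumed effect: about ±1.03 SD of change for a pair of arms, too wide to support similarity in any useful sense.

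Alpha, effect sizes, margins and correlations are assumptions. The issue concerns a secondary aim and is moderate in weight, but it is worth correcting because the correction is cheap.

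**What to change.** 1. In the Objectives, replace the similarity hypothesis with a descriptive aim: to estimate change in each arm and the differences in change between arms.
2. In Statistical methods, Outcomes, state that for each psychological outcome, whatever its p-value, the report will give mean change per arm and all six pairwise differences in change with 95% confidence intervals.
3. State that a non-significant arm-by-time test will not be taken as evidence of similarity.
4. Describe pre-post results as change from before to after treatment, in place of wording about effectiveness or about interventions leading to improvement.

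No further participants or measurements are needed. A larger sample is not the natural remedy here; if similarity is to be claimed, that belongs in a full trial with a margin set in advance. The cost is a more modest claim and a few more output tables.
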